#### Intervention

2.2.2

Two physiotherapy programs, GAITimagery and gait physiotherapy program, have been scheduled to take place over 6-week period. Each program involves two non-consecutive sessions per week, lasting 60 min each, which makes a total of 12 sessions. Additionally, this study proposes an 8-week follow-up period, which extends beyond the intervention phase. The rationale for this design is based on evidence that the benefits of gait exercises for PD emerge rapidly and are sustained over time, achieving short-term improvements in 12 to 14 training sessions over 2 to 4 weeks (27), which can persist for 3 to 12 months after treatment completion (30). The GAITimagery program will be performed for the GiG, while the GaG will develop the gait physiotherapy program without the MI exercises. To replicate the same conditions in both programs, the sessions will be done in groups of two people with the same PD severity according to the Hoehn & Yahr (H&Y) scale. Each program will be developed by different physiotherapists with an assistant, and supervised by a third physical therapist who checks that the walking exercises applied in both groups are the same. The sessions of both programs also have the same structure: warm-up (10′), central phase (45′), and cool-down (5′). Both interventions will be performed in a quiet environment, in a 7x13m room located in an area isolated from outside noise to promote the concentration of participants during the sessions. The warm-up and cool-down are the same in both programs. The essential aspects of physiotherapy in PD will be included in the warm-up section, related to respiratory exercises, dissociation of the shoulder and pelvic girdle, transfers and postural changes, joint mobility, balance, and strengthening (31). The cool-down part cover self-assisted stretching.

The central phase includes the gait training itself, in which the first 5′ will be dedicated to the explanation the session objectives and to applying the observation part of AO technique through previously prepared videos of Parkinsonian and normal gait. The purpose of AO in our protocol is to prepare participants who will subsequently perform MI exercises. However, as AO may have an effect on the physical performance of gait exercises by itself (32), both groups will perform the observation part at the beginning of gait training (Figure 2). Within the stipulated 5′, a laptop will be used to show a video focusing on the gait characteristic to be worked on in the session (whether spatiotemporal or kinematic), performed by a subject without pathologies. The physiotherapist will support the visual information with a theoretical explanation of the video content. Next, a video of the same characteristic will be shown but performed by a person with PD. The physiotherapist will explain to participants the features to be corrected. Finally, three additional videos will be shown where participants must say whether it corresponds to a normal or altered pattern. The active part of the AO will be carried out through the gait exercises proposed for each session. The walking exercises for both groups are related to the spatiotemporal and cinematic impairment of the Parkinsonian gait (31), hence are the following (33, 34): (1) step length increase through visual cues and circuit with obstacles of different sizes; (2) cadence control with digital metronome; (3) speed training over 1.00 m/s controlling the stride length and cadence; (4) posture correction during walking; (5) arm swing and shoulder girdle dissociation with proprioceptive and auditory cueing; (6) promotion the lower limb kinematic milestones of stance and swing phase, and (7) Dynamic balance during gait. All the gait exercises will be adapted to the severity of PD.

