**Figure 2 fig2:**

Organization of the GAITimagery and control gait program session. Both programs have the same structure with the exception of the Relaxation and Motor imagery section, which will be only performed in the GAITimagery program. AO, action observation. MI, motor imagery.

Additionally, the GAITimagery program consists of interspersing the physical exercise of walking with periods of MI in each session. Before MI practice, a relaxation exercise will carried out in supine position on a stretcher, obtaining in each session two complete cycles of 2’ of relaxation, 8′ of MI, and 10′ of physical walking exercise related to the treatment objective that is reinforced in the MI period (Figure 2). The MI exercises will consist of imaging a normal gait sequence focused on visualizing a requested movement (VMI) alternating with the focus on the sensation and muscle contraction associated with performing the movement indicated (KMI). MI and relaxation exercises will be guided by the voice of the physiotherapist, who will indicate what movement to imagine and the execution that should be evoked, based on the correction of the gait parameters previously studied in the AO period. All the instructions will be standardized and the physiotherapist will read it from a script. When the goal session is kinematic aspects of gait, the physiotherapist will simply describe to the participants the movement they should imagine, helping them to create a mental image with sufficient detail. When the session’s goal involves speed training, the vocal guidance will include a cadence of the steps, set by a digital metronome that the physiotherapist will listen to through headphones. Between the 8′ of MI guided by the physiotherapist, 30-s spaces will be given without vocal guidance so that participants can silently visualize the required exercise. In this no-guided MI interval, the imagery activity will be monitored through a question about the performance (35), to check the precision of MI (“What moment of the action indicated are you in right now?”). Additionally, at the end of each MI block, the participant will give feedback through two Likert-type questions (36, 37) related to the MI exercise performed (“How difficult was it to visualize the imagery exercise you just completed?” and “How difficult has it been to experience the sensations evoked in the imagery exercise you just performed?”) (Figure 3).

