A two-factor mixed Multivariate Analysis of Variance (MANOVA) will be conducted to analyze the factors effects on the outcomes registered at t0, t1, and t2. The within-subject factor is *Time* with three categories (Baseline, Postintervention and Follow-up). The between-subject factor is *Group* with two categories (GiG and GaG). When significant effects are found, Bonferroni will be used for post-hoc comparisons. Differences shall be declared statistically significant if *p* < 0.05. Before the referred statistical analysis above, the following assumptions will be checked: (1) Normality: the distributions of the residuals will be tested using the Shapiro–wilk test; (2) Sphericity: the homogeneity between variances of the differences between pairs of measures will be checked with the Mauchly sphericity test; (3) Homoscedasticity: homogeneity of variances will be evaluated using the Levene test; (4) Equality of covariance matrices: the equality of variance–covariance matrices across the cells formed by the between-subjects effects will be tested with the Box’s *M* test; (5) Absence of multicollinearity, the correlation level between dependent variables will be observed with the Pearson correlation test. If any of these assumptions are not met, the necessary statistical corrections will be used (61).

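### Participants train in twos under physiotherapists who differ by arm, but the sample size and primary model treat participants as independent and therapist is nested in arm

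*Protocol article*

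**What the plan says.** Section 2.2.2 (Intervention) sets the delivery. On staffing: "Each program will be developed by different physiotherapists with an assistant, and supervised by a third physical therapist", the supervisor being the person "who checks that the walking exercises applied in both groups are the same". On the treatment unit: "the sessions will be done in groups of two people with the same PD severity according to the Hoehn & Yahr (H&Y) scale". The paragraph after Figure 2 in the same section, which describes the relaxation and MI guidance given only to the GAITimagery group (GiG), adds: "All the instructions will be standardized and the physiotherapist will read it from a script".

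Section 2.2.4 (Sample size and recruitment) takes F = 0.15, 80% power, 5% type I error and a design of 2 groups by 3 times. It arrives at 74 participants and mentions no allowance for clustering.

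Section 2.4 fixes the model: "A two-factor mixed Multivariate Analysis of Variance (MANOVA) will be conducted to analyze the factors effects". Time is the within-subject factor. On the other factor it says: "The between-subject factor is *Group* with two categories (GiG and GaG". The possible covariates named in the Discussion are sessions completed, medication timing, disease stage, sex and level of daily activities. Neither therapist nor pair is among them.

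The primary endpoint is gait speed at the post-training visit, t1 (section 2.2.3).

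**The concern.** Participants are randomized individually but treated in twos, so partners share a therapist, a room, explanations and feedback. If this makes their outcomes alike, 74 participants carry less information than 74 independent ones, and a model with Group as its only between-subject factor understates the standard error.

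Therapist raises a different problem. Because the two programmes have different physiotherapists, a therapist's skill, encouragement or way of adapting exercises falls wholly within one arm. The trial exists to isolate what MI adds when everything else is held equal, so a therapist difference could mimic an MI effect or hide one.

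The article fixes both the staffing and the model, so this is not detail left to an analysis plan.

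**Working it through.** **Step 1. Reproduce the planned 74.** Inputs from section 2.2.4: f = 0.15, alpha 0.05, power 0.80, 2 groups, 3 times. Assumed, because not stated: correlation between times 0.5 and sphericity (epsilon 1). For the within-between interaction:

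- λ = f² × N × 3 / (1 − 0.5) = 0.0225 × 74 × 3 / 0.5 = 9.99
- df = 2 and 2 × (74 − 2) = 144
- power = 0.806 at N = 74, and 0.795 at N = 72

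So 74 is reproduced exactly with every participant counted as independent (design effect 1). Other assumed correlations give other totals (102 at 0.3, 46 at 0.7). The match therefore supports, but does not alone prove, that no allowance was made. The section mentions none.

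**Step 2. Pairs.** Here ICC means the within-pair correlation of the quantity tested: t1 gait speed given baseline, or the change over time. With m = 2, the design effect is DE = 1 + (2 − 1) × ICC. The true standard error is √DE times the nominal one. True two-sided type I error of a nominal 5% single-contrast test is 2 × [1 − Φ(1.96/√DE)]. Power is recomputed with λ = 9.99/DE. The ICC values are assumed.

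| Pair ICC | DE | SE ratio | Effective N (74/DE) | Type I error | Power at 74 | Evaluable N for 80% |
|---|---|---|---|---|---|---|
| 0.05 | 1.05 | 1.025 | 70.5 | 0.056 | 0.79 | 78 |
| 0.10 | 1.10 | 1.049 | 67.3 | 0.062 | 0.77 | 82 |
| 0.20 | 1.20 | 1.095 | 61.7 | 0.074 | 0.73 | 90 |

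The last column is 74 × DE rounded up to an even number. The table assumes that the same two people stay together. Changing partners or single attenders would alter it.

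**Step 3. Therapist.** With one therapist per arm and n = 37 evaluable per arm, the variance of the arm comparison relative to what the model estimates is (1 − ICC + n × ICC)/(1 − ICC). For an assumed therapist ICC:

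- 0.01: (0.99 + 0.37)/0.99 = 1.374, SE ratio 1.17
- 0.05: (0.95 + 1.85)/0.95 = 2.947, SE ratio 1.72

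These show only that a small therapist effect would matter. With one therapist per arm, therapist and Group are the same variable, so the therapist variance cannot be estimated and neither a larger sample nor a model term repairs it.

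**Step 4. Which model term works.** If a pair intercept u is constant over t0, t1 and t2, then (t1 value + u) − (t0 value + u) no longer contains u. A constant pair intercept thus drops out of the Group × Time contrast. Shared-session correlation arises after baseline, so the pair effect must act on the t1 outcome or vary by time.

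**The case against.** **The staffing is less certain than it looks.** A reader might infer exactly one therapist per arm and conclude that MI and therapist are inseparable. The only support is that the supervisor is called the third therapist. The same sentence uses a plural for the treating physiotherapists and gives no number per arm. What stands on either reading is nesting.

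**A single inflated type I error for therapist is not supported.** Suppose a baseline-adjusted test with residual variance factor 0.75 (assumed), so that nominal SE² = 2/37 × 0.75 = 0.0405, and add 2 × ICC/k for k therapists per arm. For therapist ICC 0.01, 0.02 and 0.05 this gives about 11%, 16% and 29% with one therapist, 8%, 11% and 19% with two, and 7%, 9% and 15% with three. The Step 3 ratio, without baseline adjustment, gives about 9%, 14% and 25% with one. The result depends on an unstated count, assumed ICCs and, for the first three sets, a test the protocol does not specify. With one therapist per arm the problem is confounding, not a calibrated error rate.

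**Stable pairs are not stated.** Section 2.2.2 does not say that the same two people stay together for all 12 sessions. Similarity due only to Hoehn & Yahr (H&Y) matching is balanced by the stratified randomization and does not make the standard error too small. Only the shared-session part does.

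**There are safeguards.** Raters are blinded and separate from treating staff, gait speed is instrumented, the hypothesis is withheld from therapists, session structure and observation videos are common to both arms, and walking exercises are checked for equality. These narrow the room for therapist effects. They do not remove nesting: the supervisor's stated check covers the walking exercises, and the script appears in the description of the MI and relaxation guidance, which controls do not receive.

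**Conclusion.** The concern holds in a limited form. Therapist is nested in arm, sessions are run in twos, and neither the sample size nor the model reflects this.

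The pair effect is modest and conditional on a positive post-baseline correlation: over the assumed ICC range of 0.05 to 0.20, the standard error is 2.5% to 10% too small.

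The therapist effect is potentially larger, but its size cannot be derived from the documents. Whether it is wholly inseparable from MI depends on whether one or several therapists treat each arm. The documents show neither that the result will be biased nor by how much the error rate will rise through therapists.

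**What to change.** 1. **Delivery records.** Keep pair membership fixed where possible, and record pair and therapist identifiers for every participant. Cost: two database fields and some scheduling effort.
2. **Primary model.** For gait speed, replace the mixed MANOVA with a linear mixed model for the t1 value, adjusted for baseline gait speed, with a random pair effect. If all three times are modelled, use a pair-by-time random effect. A constant pair intercept is not enough (Step 4). H&Y stage, already listed as a possible covariate, can enter the same model so that the pair term does not absorb similarity due to matching. Cost: a change of model for the primary outcome and a slightly wider confidence interval.
3. **Therapist.** State how many therapists treat each arm. If more than one, fit a therapist effect as well. If only one, limit the conclusion to the programme as delivered by its therapist, and say so. Cost: none beyond the wording.

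Rotating therapists between programmes by recruitment batch would let each deliver both and make a therapist term estimable. It is an option for the sponsor to weigh, not a required correction. Imagery wording could carry over into control sessions, and therapists who deliver both programmes could infer the hypothesis that section 2.3 withholds from them.

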**Figure 2 fig2:**

Organization of the GAITimagery and control gait program session. Both programs have the same structure with the exception of the Relaxation and Motor imagery section, which will be only performed in the GAITimagery program. AO, action observation. MI, motor imagery.

Additionally, the GAITimagery program consists of interspersing the physical exercise of walking with periods of MI in each session. Before MI practice, a relaxation exercise will carried out in supine position on a stretcher, obtaining in each session two complete cycles of 2’ of relaxation, 8′ of MI, and 10′ of physical walking exercise related to the treatment objective that is reinforced in the MI period (Figure 2). The MI exercises will consist of imaging a normal gait sequence focused on visualizing a requested movement (VMI) alternating with the focus on the sensation and muscle contraction associated with performing the movement indicated (KMI). MI and relaxation exercises will be guided by the voice of the physiotherapist, who will indicate what movement to imagine and the execution that should be evoked, based on the correction of the gait parameters previously studied in the AO period. All the instructions will be standardized and the physiotherapist will read it from a script. When the goal session is kinematic aspects of gait, the physiotherapist will simply describe to the participants the movement they should imagine, helping them to create a mental image with sufficient detail. When the session’s goal involves speed training, the vocal guidance will include a cadence of the steps, set by a digital metronome that the physiotherapist will listen to through headphones. Between the 8′ of MI guided by the physiotherapist, 30-s spaces will be given without vocal guidance so that participants can silently visualize the required exercise. In this no-guided MI interval, the imagery activity will be monitored through a question about the performance (35), to check the precision of MI (“What moment of the action indicated are you in right now?”). Additionally, at the end of each MI block, the participant will give feedback through two Likert-type questions (36, 37) related to the MI exercise performed (“How difficult was it to visualize the imagery exercise you just completed?” and “How difficult has it been to experience the sensations evoked in the imagery exercise you just performed?”) (Figure 3).

**Figure 3 fig3:**
[figure not shown]
Vividness control of motor imagery exercises. The items aims to control whether the GAITimagery program participants are being able to carry out the motor imagery exercises effectively.

Finally, in each physiotherapy session, the time elapsed since the last intake of antiparkinsonian medication for each GiG and GaG participant will be recorded. Likewise, the number of sessions completed during the program will be noted for each person.

#### Outcomes and participant timeline

2.2.3

The participants will be evaluated in ON-medication state (1 h after the dopaminergic dose) on the schedule described in Figure 1. Two physiotherapists will perform the assessments, which are different from the treating therapists, and blinded to the group assignment. After signing informed consents, a neurological clinical interview for PD (38) will be performed during the eligibility screening (−t1), in addition to the register of the anthropometric data lower-limbs length (during standing position from the anterior superior iliac spine to the medial malleolus), weight, and height. For this purpose, a wall stadiometer and a TANITA SC-240MA scale will be used. Also, at -t1, the severity of the disease will be evaluated with Hoehn & Yahr (39), its modified version (40), and the Movement Disorders Society Unified Parkinson’s Disease Rating Scale (41), as well as the cognitive status through the Montreal Cognitive Assessment (42, 43) and the MiniMental Parkinson Test (44).

During baseline (t0), post-6-week-training (t1), and follow-up (t2) will be measured (Table 1): (1) Perception of health-related quality of life due to PD using the Parkinson disease questionnaire (45, 46); (2) Activities in daily life employing the Schwab & England scale to indicate the percentage of functional independence in the performance of basic and instrumental activities of daily living (47, 48); (3) Freezing of gait by means of the Freezing of gait questionnaire (49); (4) Clinical performance of gait evaluated using the Tinetti mobility test and the Dynamic Parkinson gait scale (50, 51); (5) Dynamic balance assessed with the Tinetti mobility test and the MiniBEST test (50, 52); (6) Functional mobility evaluated with Timed up and go test (53); and (7) Biomechanical gait pattern measured with instrumental techniques to record spatiotemporal, kinematic, and kinetic variables (Table 1). In this respect, to record the ground reaction forces and gait speed during walking, it will be used a dynamometric platform (Dinascan/IBV Biomechanics Institute of Valencia, Valencia, Spain) and the NedAMH®/IBV software (version 5.5.0, Biomechanics Institute of Valencia, Valencia, Spain), which uses two red-light photocells too. The dynamometric platform (Figure 4A) is located in a 8 meter-walkway, in which the participants will have to walk barefoot (socks only) at self-select comfortable speed until completing at least 10 repetitions, to obtain 5 registers with each footprint. On the other hand, to record kinematics parameters of gait (Table 1), 7 Magneto-inertial measurement units (IMU) XSENS DOTs (XENS, Enschede, The Netherlands) will be employed along with their application for mobile phones to manage the measurement record (Movella DOT, version 2023.6.1). Each IMU includes a ± 2000°/s 3-axis-gyroscope, ±16 g 3-axis-accelerometer, ±8 Gauss 3-axis-magnetometer, has a dimension of 36.3 × 30.35 × 10.8 mm, and weighs 11.2 g. The gait assessment with IMUs will be carried out at the same time as the dynamometric measure. The IMUs set will be placed on the lumbar zone, thighs, legs, and feet segments, as Figure 4B shows, attached by elastic straps provided by the manufacturer to prevent them from slipping. The instruction to initiate the gait register will be given to the participants 3 seconds after starting the registration with the mobile app, through the command “start walking.” At the end of the walkway, participants will be instructed to remain standing for three other seconds, after which the recording with the IMUs will be stopped. All raw data from IMUs will be processed with Python (Python Software Foundation, version 3.7.17, 2023) to obtain the outcomes in Table 1.

**Table 1 tab1:** Summary of outcomes, measurement instrument, and assessment times.

Domain / Outcomes	Measurement instrument	Study period			
		-t1	t0	t1	t2
Informed consents		x			
Anamnesis					
Personal information	Clinical interview for Parkinson’s disease	x			
Habits and working life		x			
Disease start and initial sign		x			
Parkinson’s disease severity	H&Y; modified H&Y; MDS-UPDRS-III	x			
General cognitive state	MMP; MoCA	x			
Eligibility screen	Participant criteria	x			
Anthropometric data (weigh, height, and lower limb length)	Wall stadiometer, TANITA SC-240MA scale, and tape measure	x			
Quality of life					
Activities of daily life	Schwab & England scale		x	x	x
Perception of QoL due to PD	PDQ-39		x	x	x
Gait clinical performance					
Freezing of gait	FOG-Q		x	x	x
Gait	TMT gait; DYPAG		x	x	x
Dynamic balance	TMT balance; MiniBEST test		x	x	x
Functional mobility	TUG		x	x	x
Gait biomechanical performance					
Speed (m/s) _Primary outcome_	Dynamometric platform		x	x	x
Speed variability _Secondary outcome_					
Maximum gait speed (m/s) _Secondary outcome_			x	x	x
Stance time (s)			x	x	x
Weight-acceptance GRF (*N*; weight%)			x	x	x
Midstance GRF (*N*; weight%)			x	x	x
Push-off GRF (*N*; weight%)			x	x	x
Breaking GRF (*N*; weight%)			x	x	x
Propulsion GRF (*N*; weight%)			x	x	x
Cadence (steps/min)	Magneto-inertial measurement units		x	x	x
Stride and step length (m)			x	x	x
Stance and Swing phase (s; gait cycle %)			x	x	x
Double support time (s; gait cycle %)			x	x	x
Range of motion of lower limb joint (°)			x	x	x
Maximum ankle dorsiflexion during swing (°)			x	x	x
Maximum knee flexion during swing (°)			x	x	x
Maximum hip extension during stance (°)			x	x	x
Maximum hip flexion during swing (°)			x	x	x

H&Y, Hoehn y Yahr scale; MDS-UPDRS-III, Movement Disorders Society Unified Parkinson’s Disease Rating Scale, part three; MMP, Minimental Parkinson test; MoCA, Montreal Cognitive Assessment; PDQ-39, Parkinson disease questionnaire; FOG-Q, Freezing of gait questionnaire; TMT, Tinetti mobility test; DYPAG, Dynamic Parkinson gait scale; TUG, Timed up and go test; GRF, Ground reaction force.

